### Analysis of intervention implementation cost

In addition to testing the intervention efficacy, we will estimate the costs of planning and implementing the described mindful walking intervention using valid methods following the Consolidated Health Economic Evaluation Reporting Standards (CHEERS) 2022 framework [95]. The total program cost is undertaken from two perspectives. First, the payer perspective (the program implementer, but could be a health insurer in the future), and second, the societal perspective. Broadly speaking, the payer perspective includes all costs required to implement the program. We will collect information for all program costs but delineate in our analysis those costs that are solely research related. The research-related costs may not be relevant if the intervention is translated for further roll-out in non-research settings. The societal perspective includes payer costs and participation costs in terms of time and money, such as travel costs to attend the visits and walking sessions.

Specifically, the cost analysis is conducted prospectively with resource use and associated costs captured using micro-costing methods [96]. First, the research team tracks all non-labor costs to implement the intervention. These include, but are not limited to, charges such as transportations borne by the program, activity monitors, supplies, parking, and printing and mailing. Each team member also keeps track of research-specific (e.g., conducting outcome measures) vs. non-research costs (e.g., parking, sending reminders) to delineate costs for future translation into practice. The separation of research and non-research intervention implementation components can increase translation potential.

Second, the team will complete daily logs of time effort throughout the study period to calculate labor costs. Time effort is separated into research and non-research-related categories (e.g., delivering the intervention). This tracked time effort information will be multiplied by staff’s hourly wage/income levels to calculate the estimated labor costs (i.e., unit of time × resource cost/unit of time = labor costs). The labor and non-labor costs comprise the payer perspective (e.g., Blue Cross Blue Shield). To determine the societal costs, we survey participants at baseline and after study completion to understand their participation costs. These costs include, but are not limited to, transportation and time associated with traveling to participate in the study. Given the age of our study population and the walking session protocol, we assume no wages are lost due to retirement or that they are participating outside of work hours or during breaks. Our baseline demographic survey on retirement status and the walking session time logs will determine if our assumption holds. In addition, our participants may have transport costs such as a ride-share, public transport, or other means.

Final cost outcomes will be framed in terms of cost per participant from the payer (or program implementation) perspective and cost per participant from the societal perspective (including participant-borne costs).

***Process measures and program evaluation***. Throughout the study period, the research team will track participants in both groups to document if they attend their scheduled visits for measurement and comply with the EMA (activity and cognition monitoring) protocol. The team will track the walking session attendance and completion rates for the mindful walking group. The number of no-show events, missed sessions, rescheduled sessions, and partially completed sessions will be documented for each participant. Participants in the intervention group will complete a brief evaluation survey during the final lab visit to evaluate and refine this mindful walking study. This survey asks participants to rate program acceptability, usefulness, satisfaction, and overall value of the program using a 7-point Likert scale ranging from 0 (not at all) to 7 (very much).

**Evaluate program recruitment and retention**.

To promote participation and study compliance among AA older adults, our team also quantifies successful strategies for intervention refinement. During the recruitment phase, participants are asked to report how and where they became aware of the program. The team tracks and quantifies monthly enrollment for each recruitment activity. Following the completion of all the mindful walking sessions (after 12 weeks), we will categorize recruitment avenues (e.g., via flyers, emails, word of mouth) and local sites (e.g., churches, senior centers, local partners) and calculate percentages for those screened, not interested, ineligible, and enrolled, respectively. These percentages are calculated among the recruited sample and are broken down by key demographics (e.g., sex, employment, education level). We will compare enrollment yields by avenues and sites using a crosstab table and conduct chi-square test or Fisher’s exact test (if cell frequencies < 5) to determine if any categories of the recruited numbers are significantly higher or lower than the expected values. Identifying the highest- and lowest-yielding recruitment sources, especially for hard-to-reach minority populations, will make considerable contributions to informing recruitment strategies used in future behavioral intervention programs [97–99]. The program retention rate will be calculated post-program (after 12 weeks) and on each follow-up occasion (after 18 and after 24 weeks). The percentages of specific reasons for attrition (e.g., loss to follow-up, no longer interested, medical reasons) will be calculated among the total sample and by demographics. We will further collect the retention rate and reasons for attrition based on the recruitment avenues and sites. The chi-square test (or Fisher’s exact test) again will examine differential attrition rates using a crosstab table.

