### Recruitment

This study engaged with community partners who share the same mission to promote healthy aging and address ADRD in older populations (e.g., SC AARP, SC Alzheimer’s Association Chapter, SC Department on Aging). These local partners have rich experience interacting with underrepresented racial and ethnic groups, so they are assisting in recruiting our priority population of AA participants. They also serve on our community advisory board (CAB) to provide insights and feedback on the planning, outreach, recruitment, and implementation of the mindful walking program.

In addition to the community-engaged recruitment approach, we also leverage the SC Alzheimer’s Disease Registry, the Dementia Dialogues® Certified Instructors in SC, and the Office for the Study of Aging’s (OSA) listserv, all hosted by the OSA at the University of South Carolina. The ADRD registry is the most comprehensive database among the only three population-based registries in the US [48]. Our study does not recruit older adults with cognitive impairment, but this unique platform can help us identify eligible AA older adults by sending out promotional materials/mailers to the homes of individuals with ADRD to inform eligible family members and caregivers. Normally, the family members or caregiver(s) of the care recipient in the ADRD registry monitor the mails and they likely meet the inclusion criteria to participate in this study. Other general recruitment methods are also carried out by the research team, including distributing fliers and mailers at community events, senior living facilities, local churches, and retirement centers. We also send out electronic flyers to relevant email listservs, online forums/support groups, and paid public service announcements. The study recruitment has occurred on a rolling basis and will continue until May 2024.

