**Device-based measure of daily movement activity.**

This study applied the research-grade activPAL accelerometer (PAL Technologies, Glasgow, UK) to measure physical activity outcomes in both groups during the four measurement bursts that overlap with the mobile cognitive assessment period. ActivPAL is a valid and reliable accelerometer to capture subtle changes in posture (e.g., sitting, standing) and movement (e.g., stepping) among older adults in free-living contexts [78–80]. During each measurement burst, participants wear the activPAL on the thigh for 24 h a day, including sleep time but excluding bathing or swimming time. A copy of the activPAL wearing instructions is provided to participants at their baseline visit.

In the activPAL output file, accumulated steps and minutes of light, moderate, and vigorous physical activity are summarized across all waking hours for each wear day [81]. In this study, the time spent in different intensities of physical activity (i.e., light, moderate, or vigorous) is determined by the activPAL ActivityScore (MET.h) value (a proxy index of energy expenditure levels) with reference to the CDC metabolic equivalents (METs) cutoff values [82]. This device-based data compares physical activity levels (and steps) between the two groups before, during, and after the mindful walking intervention.

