Cost analyses are rare in the behavioral intervention literature, but we track this critical information for future implementation, sustainability and scale-up. This study estimates the time and personnel effort to allow organizations or private institutes to budget the cost required to implement this community-based program [108]. If sufficient evidence suggests the efficacy of this mindful walking on cognitive health and its costs are known, it can be introduced to government agencies or federal health insurance programs and their relevant benefit packages (e.g., State Department of Parks, Recreation and Tourism, Medicare Advantage, and other Medicare plans). Evidence to support payer decisions to adopt such a program in their benefit packages will allow for broader community dissemination. It can also enable the incorporation of this program into existing older adult physical activity programs to promote healthy brain aging and active lifestyles.

The last follow-up assessment is scheduled for 12 weeks post-intervention (24 weeks from baseline) due to constraints in the funding timeline. The duration of this follow-up may not be sufficient to capture the occurrence or diagnosis of neurodegenerative diseases among our participants. However, this study aims to detect program efficacy using sensitive measures of cognitive change or decline to study the between-group differences [57, 63, 109]. This study does not attempt to compare the occurrence of brain diseases or symptoms between the two groups after the intervention. The success of this study will inform future work to extend the follow-up period across years to understand whether mindful walking reduces the likelihood of developing any neurodegenerative diseases among at-risk older adults.

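### The payer cost per participant is not fixed as the cost an adopter would bear: labour is priced at hourly wage, outcome monitors are listed as an implementation cost, and research costs are not expressly removed

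*Protocol article*

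**What the plan says.** All of the costing rules are in the protocol article under 'Analysis of intervention implementation cost'.

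- **Labour quantity.** "the team will complete daily logs of time effort throughout the study period to calculate labor costs". The time is sorted into research and non-research work.
- **Labour price.** The logged time is multiplied by staff "hourly wage/income levels to calculate the estimated labor costs". A parenthesis restates this as "unit of time × resource cost/unit of time = labor costs".
- **Non-labour items.** The costs tracked as those of implementing the intervention include "charges such as transportations borne by the program, activity monitors, supplies, parking, and printing and mailing". The list is open-ended.
- **Research split.** Costs that are purely research-related are to be delineated in the analysis, because they may not matter on roll-out. Conducting outcome measures is the example given of a research-specific cost. Parking and reminders are the examples of non-research costs.
- **Payer total.** The payer perspective is said to cover everything needed to implement the programme. It is later described as made up of the labour and non-labour costs, with an insurer as the example. The final outcome is a cost per participant on that perspective, and another on the societal perspective.

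Two other sections bear on this. 'Device-based measure of daily movement activity' says the activPAL is used "to measure physical activity outcomes in both groups during the four measurement bursts". The Discussion states the purpose of the costing: "This study estimates the time and personnel effort to allow organizations or private institutes to budget the cost required to implement this community-based program".

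**The concern.** The figure is meant for organisations and payers deciding whether they can afford the programme. For that use it should contain what an adopter would pay and nothing that only the trial needed. Three features of the text work against this.

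1. An employer pays more than the wage, and the stated unit price is wage or income.
2. A measurement device sits in the list of implementation costs, against the section's own rule for what counts as research.
3. The sentence defining the payer total does not say whether research costs are in or out, so two different headline figures fit the text.

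Labour is likely to be a main input. Each intervention participant has 24 individual staff-supervised sessions, and the team makes weekly check-in calls. The choice of labour unit price therefore matters.

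**Working it through.** The article gives no wage, staff hours, monitor price or cost per participant, so there is no figure of the plan's own to reproduce. What can be checked is the effect of the labour rule as a formula, and whether the passages agree.

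**1. Labour unit price**

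Let w be the bare hourly wage, f the on-costs (benefits and payroll charges) as a fraction of wage, and H the logged hours.

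- Cost under the stated rule, if the rate is bare wage: H × w
- Cost borne by the employer: H × w × (1 + f)
- Understatement as a share of the employer's cost: f / (1 + f)

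The article does not give f. With an assumed range:

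| f | Calculation | Labour understated by |
|---|---|---|
| 0 (rate already includes on-costs) | 0 / 1 | 0% |
| 20% | 0.20 / 1.20 | 16.7% |
| 40% | 0.40 / 1.40 | 28.6% |

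As a sense of scale, supervised walking time alone is 24 sessions × 0.5 h = 12 h per intervention participant ('Outdoor mindful walking sessions'). The missing on-costs on those hours are worth 12 × 0.20 = 2.4 to 12 × 0.40 = 4.8 wage-hours. Set-up, demonstration, post-walk interviews and phone calls come on top, and the article does not quantify them.

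**2. Activity monitors**

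- The cost section lists monitors under implementing the intervention.
- That list reads as the implementation category: parking appears in it and is also the section's example of a non-research cost.
- The activPAL's stated use is to measure outcomes in both arms. The description of the walking sessions gives the device no part in delivering them.
- The section's own example of a research-specific cost is outcome measurement.

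The last two points put monitors in research; the first two put them in implementation. If M is the monitor cost per participant (not given), the overstatement is 0 when monitors are classed as research and M when they stay in the implementation total.

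**3. The payer total**

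Per participant, let L be non-research labour at bare wage, N the non-research non-labour cost without monitors, M the monitors, and R all other research cost.

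- Labour plus non-labour, nothing removed: L + N + M + R
- Research removed, but monitors left in implementation: L + N + M
- What an adopter would bear: L(1 + f) + N

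The first differs from the last by M + R − fL, and the second by M − fL. Either difference can be positive, negative or near zero, and none of M, R, L or f is given. The net direction is therefore open.

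**The case against.** **The research split already deals with the monitors.** The section promises to delineate research costs and tags both costs and staff time accordingly, so a measurement device should end up under research. The sentence on the payer total only names components and need not withdraw that promise. This is a fair reading and may be what is intended. It stands to the extent that no error in a final figure is proven. It does not remove the conflict: monitors are placed by name on the implementation side, and the text never says that the headline is net of what has been delineated.

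**The monitors do more than measure.** The 'Adherence plan' gives participants a summary of their activity from the device. It appears there as part of promoting retention in the study, so it does not make the monitor an implementation cost.

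**The wage wording does not exclude on-costs.** The parenthetical formula uses a wider term, and an article may leave such detail to the full protocol. However, the parenthesis is introduced as a restatement of the wage calculation. The unit price is thus stated, and it is narrower than the section's own scope for the payer perspective. What stands is that the error is zero if the recorded rate already carries on-costs.

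**Cost is not an efficacy outcome.** True: no primary or secondary outcome depends on it. That limits the weight of the point.

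**A stronger reading: unpriced partner time.** A reader might infer that community partners' and advisory-board members' time is wrongly left out, since the partners' experience is described as useful "so they are assisting in recruiting our priority population of AA participants" and only the team keeps logs. The documents do not support calling this an error. Part of that effort is recruitment into the trial, the board's role is to give insight and feedback, and nothing says the programme pays for the time. Whether to price it is a choice of perspective.

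**Conclusion.** The point holds as a defect in how the payer cost is defined. Taken as bare wage, the labour rule understates the payer's labour cost by about 17% to 29% if on-costs are 20% to 40% of wage, and by nothing if the recorded rate already includes them. The on-cost range is an assumption. The classification of activity monitors conflicts with their stated use and with the section's own research rule. The payer total does not state that research costs are removed.

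A reader might go further and infer that the cost per participant will be too low on labour and too high on equipment. The documents do not establish that. They contain no cost inputs or results, the promised research split may already take the monitors out, and the wage may be recorded with on-costs. Neither the size nor the net direction of the effect on the headline can be derived. The budgeting use stated in the Discussion is what makes the definition worth settling; no efficacy conclusion is affected.

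**What to change.** Make three changes in 'Analysis of intervention implementation cost':

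1. Value each logged hour at full employment cost (wage plus benefits and payroll charges), and report the bare-wage result as a sensitivity figure.
2. Classify activity monitors as a research cost, in line with the section's rule on outcome measurement.
3. Define the headline payer cost per participant as non-research labour plus non-research non-labour, and show the research total separately.

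The cost is small. Time and resource use are already collected prospectively with research and non-research tags, so the work is a different unit price, one reclassified line and one sentence of definition. No arm, visit or outcome changes. The downside is a somewhat higher, less favourable labour cost.

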### Follow-up lab visits

At the post-intervention visit after completing the last mindful walking session at week 12, participants in both groups meet with the research staff to complete in-lab assessments that are identical to the baseline measures (except the demographics surveys). Participants in both groups also meet with the research staff for two follow-up in-lab assessments after 18 and 24 weeks to evaluate the longer-term intervention effects. On the last visit, participants can provide their feedback on the study, and they will receive monetary compensation based on their compliance (up to $200).

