### Data preparation, analysis, and management

***Power and sample size consideration***. We conduct apriori power and sample size calculation to detect at least a small between-group effect (Cohen’s *d* = 0.2) based on the available literature showing the anticipated effect sizes from mindfulness-based physical activity programs and cognitive health in older adults [84–86]. The power analysis R package “powerlmm” is used to determine the sample size in the mixed-effects analysis framework with repeated measures. The package identified that a total sample size of 114 participants (57 in each group) would support the detection of the pre-specified small effect size between two groups with sufficient power (≥ 0.80) [87]. We plan for a 15% dropout rate based on the attrition rate in our preliminary study and the annual injury rates (~ 5%) in older adults (i.e., due to serious falls) that lead to unanticipated dropouts [88]. Thus, we will recruit 18 extra participants to account for the attrition, so the actual power for analysis is likely to be greater.

***Statistical analysis***. After the study is completed, we will first examine the distributions of all the quantitative outcome variables prior to any statistical analysis. If any variables violate the normal distribution assumption, we will apply proper sampling distributions and link functions to model the data [89]. We will apply the generalized linear mixed-effects modeling to examine the short- and longer-term effects of mindful walking on cognition and other study outcomes. The repeated measures collected across the study period are the within-subject components, and the group allocation (mindful walking vs. delayed walking group) is the between-subject component in the model. The primary interest in the model is the Time x Group interaction term, which will determine whether significant differences exist in the outcomes between the two groups from baseline to post-intervention. The analyses will be conducted in R program version 4.0.1 [90]. Participants’ baseline characteristics and demographics (e.g., sex, age, BMI, general health status, etc.) will be adjusted in all models. We will also control for participants’ enrollment time of the year (in months) in our analyses to account for any potential seasonal effects that may impact the study outcomes.

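### Acceptability ratings and incurred participant costs are collected only at the end of the study, so walkers who leave earlier supply neither

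*Protocol article*

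**What the plan says.** All references are to the protocol article.

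- **Evaluation survey.** Under Analysis of intervention implementation cost (process measures paragraph): "Participants in the intervention group will complete a brief evaluation survey during the final lab visit to evaluate and refine this mindful walking study". On content: "This survey asks participants to rate program acceptability, usefulness, satisfaction, and overall value of the program using a 7-point Likert scale". The scale is described as "using a 7-point Likert scale ranging from 0 (not at all) to 7 (very much").
- **Which visit is final.** Follow-up lab visits provides for "two follow-up in-lab assessments after 18 and 24 weeks to evaluate the longer-term intervention effects", so the final visit is week 24. The Discussion confirms the interval: "The last follow-up assessment is scheduled for 12 weeks post-intervention (24 weeks from baseline").
- **Participant costs.** For the societal perspective, "we survey participants at baseline and after study completion to understand their participation costs". These costs are added to payer costs to give a societal cost per participant.
- **Expected loss.** The power paragraph states: "We plan for a 15% dropout rate based on the attrition rate in our preliminary study". It adds that "we will recruit 18 extra participants to account for the attrition". The Adherence plan lets participants leave at any time without giving a reason.

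**The concern.** The only structured measure of how acceptable, useful, satisfying and worthwhile walkers found the programme is taken from those still present 12 weeks after it ended. A walker who found it tiring, unhelpful or hard to reach, and who left the study for that reason, is among the most informative people for refining it and gives no rating. The recruitment and retention section itself lists loss of interest among the attrition reasons to be tabulated.

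The cost survey has the same weakness. Baseline comes before randomisation and before any trip to a walking session, so it cannot record session travel actually incurred. The later survey reaches those who are retained, and asks them to recall travel to as many as 24 sessions.

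At stake are an acceptability rating that may be too favourable and a participant-borne cost that may reflect fuller attendance than the randomised group had. Both are stated choices about when to measure, and a visit placed directly after the programme (week 12) already exists.

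**Working it through.** **Inputs from the article:** 114 participants, 57 per group; 15% planned dropout; 18 extra recruits; survey at week 24; cost survey at baseline and after completion.

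**Inputs that are assumptions:** the 15% applies equally to the walking group; the gap in rating between stayers and leavers; the share of a completer's participant-borne cost that a leaver incurs. The article gives no figure for any of these.

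**1. The plan's own figure.** 114 × 0.15 = 17.1, rounded up to 18 extra, so 114 + 18 = 132. This reproduces the stated number. Dividing instead, 114 / 0.85 = 134.1, gives 135. The difference of 3 people does not affect this point.

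**2. Walkers without a rating or an incurred-cost report.**
- 57 × 0.15 = 8.55, about 9.
- If the 18 extra are split equally, there are 66 walkers: 66 × 0.15 = 9.9, about 10.

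**3. Effect on the mean rating.** Let d be the share who leave and g the amount by which leavers would rate the programme lower. The mean among those surveyed exceeds the mean over all randomised walkers by d × g.

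| Assumed g (points on 0 to 7) | Excess at d = 15% |
|---|---|
| 1 | 0.15 |
| 2 | 0.30 |
| 3 | 0.45 |

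Over d from 5% to 25% the range is 0.05 × 1 = 0.05 to 0.25 × 3 = 0.75 points.

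**4. Effect on participant-borne cost.** Let s be a leaver's cost as a share of a completer's. If only completers' reports were averaged, the overstatement would be 1 / [(1 − d) + d × s] − 1.

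| Assumed s | Calculation at d = 15% | Overstatement |
|---|---|---|
| 25% | 1 / 0.8875 − 1 | 12.7% |
| 50% | 1 / 0.9250 − 1 | 8.1% |
| 75% | 1 / 0.9625 − 1 | 3.9% |

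These percentages apply to the participant-borne component only. The effect on the whole societal cost is smaller, because payer costs are part of it, and cannot be computed without the split between the two.

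**5. Response scale.** The integers 0, 1, 2, 3, 4, 5, 6, 7 are eight points, not seven.

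**The case against.** The strongest reply is that leavers are not invisible. Walkers complete a short survey before and after each walk and then a staff interview about their experience. Weekly calls ask about discomfort. No-shows and missed, rescheduled and partial sessions are recorded for each participant, and reasons for attrition are tabulated. This stands, but only in part. None of these sources is the stated set of ratings, attendance records count trips without pricing them, and a participant may leave without giving a reason.

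A second reply is that a condensed article may leave exit procedures to the full protocol. That is fair as regards a withdrawal questionnaire, whose absence is not held against the plan here. The point rests on the timing that the article does fix.

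Third, some loss has nothing to do with acceptability. The planned 15% allows for injuries (about 5% a year), so leavers as a group need not rate the programme much lower. This is a good reason to treat the figures above as a sensitivity range.

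Three stronger readings are tempting, and the documents do not support them:

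- A reader might infer that anyone who stops walking is excluded. Attendance and retention are tracked separately, outcomes follow intention-to-treat, and nothing bars a walker who stopped sessions from the week-24 visit.
- A reader might infer that the cost results as a whole describe completers. Payer costs come from staff time logs and tracked programme expenses, the baseline cost survey covers everyone enrolled, and the article never says costs will be averaged over completers only.
- A reader might infer that both results feed payer decisions. The Discussion ties those decisions to cost and efficacy. The acceptability survey is for evaluating and refining the programme.

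**Conclusion.** The point holds in a limited form. The structured ratings and the reports of incurred participant cost come only from walkers retained to the end of the study, and about 9 of 57 would be missing if the planned 15% dropout applies to the walking group. The direction of the bias is plausible (ratings too favourable, participant-borne cost too high) but not certain: leavers with costlier travel would offset part of the cost effect if they had made many trips. Its size cannot be derived from the documents. With gaps of 1 to 3 points and leavers incurring 25% to 75% of a completer's cost, it is 0.15 to 0.45 rating points and about 4% to 13% of participant-borne cost.

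These are process and cost results. The comparison on cognition is untouched. The change is still worth making because it uses contacts and records that already exist. The response-scale wording is a separate, minor contradiction with no bearing on who is surveyed.

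**What to change.** 1. Give the evaluation survey at the existing week-12 visit, or at last contact (by telephone if necessary) when a walker leaves the study before then. Report the number responding out of the number randomised to walking.
2. Ask for travel mode, time and cost per trip at an early walking session. Compute participant cost as unit cost × attended trips, using the attendance records already kept, for every randomised walker including those who leave.
3. Correct either the 7-point label or the anchors so that they agree: 0 to 6 or 1 to 7 gives seven points, and 0 to 7 gives eight.

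The cost is small: one short survey moves and a few travel questions are added to a contact that already takes place. The ratings may look less favourable, and the hindsight view at week 24 is lost unless the survey is repeated at that visit.
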